### **3.2 Sample Size**

Hospitalized patients fulfilling eligibility criteria at HDZ NRW or Klinikum Karlsruhe are recruited for the trial. After informed consenting wounds will be randomized to one or the treatment arm applying stratified randomization, considering patient's age, gender and smoking status. 30 wounds per group shall be analyzed. Considering a dropout rate of 10% 66 wounds in total have to be recruited.

### **3.3 Projected time schedule**

|                               |                                              |
|-------------------------------|----------------------------------------------|
| Preparation and recruitment:  | continuously                                 |
| Data analysis:                | 3 Months                                     |
| Total trial duration:         | 8 Months, incl. Follow up: 5 years, 8 Months |
| Start of study:               | July 2016                                    |
| End of study incl. follow up: | December 2021                                |

## **4 Patient selection**

### **4.1 inclusion criteria**

- Type 1 or Type 2 Diabetes mellitus
- HbA1c  $\leq 10\%$
- at least one chronic wound persisting for at least three weeks without healing tendency following standard care wound therapy (Armstrong-Wagner Grade 1B or 2B)

### **4.2 exclusion criteria**

- concomitant wound treatment with local vacuum therapy or maggot therapy
- dialysis
- use of topical active antibiotics,
- concomitant treatment with platelet rich fibrin (PRF),
- presence of critical limb ischemia defined as ankle brachial index below 0.5 or transcutaneous oxygen pressure below 15 mmHg.
- participation in another clinical trial
- women of child bearing potential without effective contraception or active breastfeeding

### **4.3 Documentation of patient data**

Before randomization eligibility criteria will be checked by the investigator. Further data documentation comprises:

- Patient's initials
- Date of birth
- gender
- background medication
- medical history
- concomitant diseases

## **5 study materials**

Patient's well-being will be evaluated at the beginning, during and at the end of the study using questionnaires (EQ5D, SF12, Visual analog scales to evaluate clinical symptoms, pain, and well-being).

At HDZ NRW wound dressings will be sampled at each visit to analyze wound healing on the level of protease, growth factors and markers of inflammation.

## **6 concomitant therapy, therapy beyond end of study**

The concomitant therapy will be recorded and updated regularly at each visit using study specific forms. Wound therapy will be monitored either. At distinguished visits wound swaps will be taken and analyzed for microbial load. At each visit the investigator will be asked to judge clinical infection of the wound upon signs and symptoms.

At the end of the treatment phase the investigator will develop an individual plan for further treatment of the patient, either in an ambulatory or clinical setting.

## **7 potential risk**

According to current knowledge application of cold atmospheric plasma is not associated with negative clinical side effects. Thus, no additional risk for the participants is to be awaited. Cold plasma therapy is used for the treatment of superficial skin diseases like acne, scars or cicatrices. Even from the therapy of tumors positive effects have been described. Cellular impairments caused by UV-radiation or thermal stress was excluded in clinical studies (7, 12). The application of cold plasma will be performed only by trained personal at both study sites. The device in use is CE-certified and licensed for the superficial skin treatment (kINPen® Med, Appendix 1).

Treatment is planned as an ad on treatment to standard wound care performed during the hospital stay of the patients. Thus, for both groups, plasma as well as placebo, no further risk is awaited. To current knowledge, patients feel no pain during treatment and potential therapy associated risks are of low occurrence.

## **8 premature discontinuation**

### **8.1 for patients**

Patients' participation in this trial is voluntarily. All patients may at any point in the trial withdraw from the trial, without giving any reasons.

Possible reasons could be:

- withdraw of consent
- exclusion by investigator due to medical reasons
- pregnancy
- inadequate compliance of the patient (e.g. Off-loading of the wound)
- violation of in- or exclusion criteria
- worsening of wound condition, affording additional treatment
- newly detected disease, affecting the study intended treatment

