| Study design                       | This study will be conducted as a bi-center, randomized, patient-blinded study with a certified medical device. For determination whether cold plasma application in patients with diabetes and diabetic foot Wagner-Armstrong stage 1B or 2B as well as ulcer curis may accelerate wound healing, people presenting with either type 1 or type 2 diabetes mellitus will be randomized to plasma or placebo therapy, respectively. Each group should be comparable according to age, gender and ulcer-stadium.                                                                                                                                                                                                                                                                                                                          |
| No. of patients/ duration of study | A dropout rate of 10% is assumed for this study. 66 patient wounds will be recruited to result in 60 evaluable data sets. Study procedures will be performed at HDZ NRW in Bad Oeynhausen and at Klinikum Karlsburg in Karlsburg. Patient wounds will be equally assigned to both treatment groups (plasma and placebo) via stratified randomization. Patient being hospitalized for treatment of diabetic foot (Wagner-Armstrong stage 1B or 2B) are in focus of the study which is carried out in a hospital setting. The study is planned to take approximately 8 months comprising 8 applications (5 on consecutive days, 3 afterwards in every second day manner). Follow up evaluations are planned after 1, 2 and 5 years after the first application to evaluate therapeutic side effects and long-term effects of the therapy. |

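### Section 8.1 lets wound worsening end trial participation, with no further measurement foreseen, so the analysed wounds may be selected on the primary outcome

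*Protocol*

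**What the plan says.** Section 8.1 is about leaving the trial: "All patients may at any point in the trial withdraw from the trial, without giving any reasons". A list follows, opened by "Possible reasons could be". It includes "worsening of wound condition, affording additional treatment", "exclusion by investigator due to medical reasons", "violation of in- or exclusion criteria" and inadequate compliance, with off-loading as the example. I read the first of these as worsening that requires additional treatment. The section says nothing about measuring a wound after any of these events.

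On numbers, the Synopsis states that "66 patient wounds will be recruited to result in 60 evaluable data sets", and section 3.2 that "30 wounds per group shall be analyzed", with a 10% allowance for dropout.

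Section 2.1 makes the changes in wound area, clinical infection and microbial load primary. Section 3.1 describes blinding of the patient only. Section 6 has the investigator judge infection at each visit. The time schedule has wound documentation and infection signs at every visit from Day 1 to Day 14, and swabs on Days 1, 5, 7, 12 and 14.

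**The concern.** A wound that gets worse is a bad result on the primary measures. If its patient then leaves the trial and nothing more is recorded, the later values are missing because of the outcome. An analysis plan can choose how to handle missing values, but it cannot restore measurements that were never taken. Whether observation continues is therefore a matter for the protocol.

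Two things can go wrong. If plasma works, more placebo wounds worsen and leave, the remaining placebo wounds look better than the arm as a whole, and the effect is understated. If the decision to withdraw is made more readily in one arm, a difference can appear where none exists. The second is possible because the protocol does not say that whoever makes that decision is unaware of the allocation.

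**Working it through.** **The plan's own figure.** 60 × 1.10 = 66, which reproduces the stated number (60 / 0.90 = 66.7 would give 67). The allowance is 66 − 60 = 6 wounds, or 3 per arm. The 30 per group cannot be derived, because no effect, SD, alpha or power is given.

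**Illustrative model.** From the protocol: 33 wounds per arm. Assumed: log ratio of final to initial area normal with SD 0.4, placebo mean −0.3, true effect ln 0.75 = −0.288 (plasma mean −0.588), independent wounds, two-sided t-test at 0.05. A wound counts as worsening if its area grows by more than 10%, that is, above ln 1.10 = 0.095.

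*Share worsening*, 1 − Φ(z):
- placebo: z = (0.095 + 0.300)/0.4 = 0.988, share 0.162
- plasma: z = (0.095 + 0.588)/0.4 = 1.708, share 0.044
- average: (0.162 + 0.044)/2 = 0.103

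*Means if all worsening wounds leave*, μ − σφ(z)/Φ(z):
- placebo: −0.300 − 0.4 × 0.245/0.838 = −0.417
- plasma: −0.588 − 0.4 × 0.093/0.956 = −0.627
- difference: −0.210 in place of −0.288. Since exp(−0.210) = 0.81, a 25% extra reduction appears as about 19%.

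*Simulated power with the true effect:*

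| Worsening wounds that leave | Mean difference | Power |
|---|---|---|
| none | −0.29 | 0.82 |
| half, both arms | −0.25 | 0.74 |
| all, both arms | −0.21 | 0.63 to 0.64 |

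*Simulated two-sided error with no effect:*

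| Removal probability, one arm vs the other | Error |
|---|---|
| 1.0 vs 1.0 | 0.05 |
| 0.5 vs 0.25 | 0.06 |
| 1.0 vs 0.5 | 0.10 |
| 1.0 vs 0 | 0.22 |

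Under no effect, the error rises here only when removal is unequal.

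**Bound that needs no SD.** Suppose all 6 allowed losses are the worst wounds and there is no effect. A placebo/plasma split of 4/2 shifts the difference by 0.10 SD against plasma, with error about 0.10. A split of 6/0 shifts it by 0.31 SD, with error about 0.26. If all 6 come from plasma, the same 0.31 SD shift favours plasma. These are upper bounds, since not every dropout would be a worst wound.

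**What the remedy delivers.** The 0.82 assumes that worsening wounds keep their untreated values. After additional treatment they would not. If these wounds instead average −0.15 at Day 14 (SD 0.4):
- placebo: 0.838 × (−0.417) + 0.162 × (−0.15) = −0.374
- plasma: 0.956 × (−0.627) + 0.044 × (−0.15) = −0.606
- difference: −0.232, simulated power about 0.73

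If they average −0.3, the same sum gives −0.398 and −0.613, a difference of −0.215, and power about 0.68.

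**The case against.** A reader might infer that only evaluable wounds will be analysed and that every wound that worsens is removed. The protocol says neither. The 60 and the 30 per group are sizing statements. The term evaluable is not defined, no analysis set is named, and no sentence excludes a withdrawn wound from analysis. Analysis sets may be set out in a SAP, which is not among the documents. The list in 8.1 is permissive, and its item on worsening is limited to cases needing additional treatment, which is narrower than any growth above 10%. All of this stands.

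Poor compliance and eligibility violations are not selection on the outcome. Compliance is a post-randomisation selection of another kind, and an eligibility violation can be a baseline fact. That also stands.

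Area values up to withdrawal would normally exist, because the wound is documented at every visit. The model deletes the wound altogether and so overstates the loss. If each worsening wound were kept with its value capped at 10% growth, power would be about 0.81.

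The model's inputs are chosen, not taken from the protocol. The match between 10.3% lost and the planned 10% follows from that choice, and it gives the whole allowance to one of seven listed reasons. Section 8.1 also speaks of patients, while section 2 randomises each wound separately. A patient with wounds in both arms would take both out, which the model ignores.

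What the objection does not remove: 8.1 ends participation and not only treatment, and no measurement afterwards is foreseen. A discretionary list does not help here, because discretion used by someone who may know the arm is what makes unequal removal possible.

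**Conclusion.** The point holds as a risk built into the protocol: the analysed wounds may be selected on the primary outcome. It is not shown that they will be, nor that the protocol prescribes an analysis of evaluable wounds only.

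The direction is not fixed. The effect is understated if placebo loses more worsening wounds and overstated if plasma does. On the stated assumptions, power falls from about 0.82 to between 0.74 (half leave) and 0.63 (all leave), and the error under no effect lies between about 0.06 and 0.10 for a twofold difference in removal. Full removal is the worst case. The figures depend on the assumed SD, means, growth cut-off and independence of wounds, none of which the protocol supplies.

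The gain in power from the remedy may be small, since 0.68 to 0.73 is not far above 0.63. Its main value is that the comparison no longer depends on who was withdrawn.

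**What to change.** 1. In section 8.1, separate the end of study treatment from the end of observation.
2. Unless consent is withdrawn, continue the scheduled area, infection-sign and swab measurements to Day 14 for every randomised wound, whatever additional treatment is given.
3. State that the primary analysis includes all randomised wounds in their allocated arm. Define the evaluable set and use it for a sensitivity analysis.
4. State that the primary estimate includes the effect of additional treatment after worsening, which may dilute the difference. Add a sensitivity analysis that uses the last area before additional treatment.

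The cost is protocol wording and the completion of measurements already in the time schedule, in patients recruited as inpatients. The trade-off is the dilution named in item 4. No change to when treatment is stopped is proposed.

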### **8.2 for the trial**

The trial may be interrupted or stopped by the principal investigator taking into account the benefit/risk-ratio.

Possible reasons are:

- New knowledge on possible risks or facts, that make a re-evaluation of benefit/risk ratio necessary, ending up in a negative result
- Occurrence of severe unexpected treatment related adverse events

## 10.1 CE-Certificate Plasma Jet

[figure not shown]

## EC Certificate of Conformity

### The Notified Body

**MEDCERT Zertifizierungs- und Prüfungsgesellschaft für die Medizin GmbH**  
**[name]**

herewith confirms that the company

**neoplas tools GmbH**  
**[name]**  
**Germany**

has introduced and applies a Quality Management System  
for the products / product categories

**Plasma devices for wound cleansing  
and therapy of skin diseases**

An Audit demonstrated compliance of the Quality Management System with

### Annex V

of the **Council Directive 93/42/EEC concerning Medical Devices.**

The certification assumes that the company is applying and maintaining its Quality Management System according to the above given annex. The license of certification is subject to surveillance by MEDCERT.

